## Abstract

**Background:**

Abdominal pain is frequent in patients consulting in emergency departments. The aim of this study is to determine the diagnosis efficacy of point-of-care ultrasound (POCUS) in patients consulting in the ED for acute abdominal pain by comparing the rate of exact diagnostic between the two arms (with or without POCUS), according to the index diagnostic established by an adjudication committee.

**Methods:**

It is a randomized, controlled, open and interventional study in two emergency departments. The included patients will be adults admitted for acute abdominal pain. Exclusion criteria will be a documented end-of-life, an immediate need of life-support therapy and pregnant or breast-feeding women. Patients will be randomized in intervention (POCUS) or control groups. POCUS will only be performed by trained physicians and will be added to the diagnosis procedure in the intervention group. In the control group, the diagnosis will be established after clinical examination and reception of biological analysis results. In the interventional group, the diagnosis will be established after a clinical exam, biological analysis reception and POCUS. An adjudication committee will review all data from case report forms and will determine the index diagnosis which will be used for the analysis.

The primary endpoint will be the comparison of the rate of exact diagnostic between the two arms according to the adjudication committee diagnostic. Secondary endpoints will be the comparison between the two groups for diagnostic delay, duration of ED stay, diagnostic performances for non-specific abdominal pain and hospitalization rate. The primary endpoint will be compared between the two groups using a mixed model taking into account the recruiting centre. Delays will be compared by a mixed linear generalized model. Diagnostic performances will be estimated with their 95% confidence intervals. For a correct diagnostic rate of 57% in the control group and 74% in the intervention group with a 0.05 alpha risk and a 80% power, 244 patients will be required.

**Discussion:**

POCUS diagnostic abilities have been mainly demonstrated in monocentric studies but the level of evidence of its diagnostic efficacy remains controversial in particular in Europe. The aim of this study is to address this question with a rigorous methodology.

**Trial registration:**

ClinicalTrials.gov NCT04912206. Registered on June 3, 2021.

## Introduction

Acute abdominal pain is one of the most frequent complaints of patients presenting to the emergency department (ED) [1]. In the US, in 2007, these patients represented 6.5% of the total ED census [1]. Acute abdominal pain can arise from many causes, including surgical, medical, and also non-specific abdominal pains [2]. Acute abdomen remains a continuing diagnosis challenge for emergency physicians (EP), even if diagnosis performance has improved over the years, especially due to the widespread availability of advanced imaging tools, such as computed tomography (CT) or ultrasound (US) [1, 3]. Currently, evaluating acute abdominal pain relies on the physical examination, laboratory tests, and in many cases, imaging procedures. In the context of limited radiology department resources, this leads to long waiting times in the ED.

Point-of-care ultrasound (POCUS), performed by clinicians at the bedside, is increasingly used in the ED [4]. Recently, it has become an integral part of the EM curriculum [5]. US is particularly suited to assess patients with acute abdominal pain as many organs are easily explored [6]. Lindelius demonstrated that a surgeon-performed US increased diagnostic accuracy in patients with acute abdominal pain [7]. Moreover, POCUS decreased short-term examinations [8] and increased patient’s satisfaction. It was also demonstrated that POCUS could result in fewer further requested examinations, fewer admissions and shorter lead times to surgery, without significant side effects [9]. Another study showed that POCUS increased diagnostic accuracy and the planned diagnostic imaging work-up in a population of 128 ED patients with non-specific abdominal pain [10]. POCUS is usually used as a first-line imaging procedure, followed by a computed tomography if needed. This strategy has been considered as the most accurate according to sensitivity and exposure to radiation [2].

In summary, POCUS diagnostic abilities have been demonstrated, in monocentric studies [2, 7, 8, 10]. However, the level of evidence of POCUS diagnostic efficiency remains controversial. We thus aimed to investigate the efficacy of an early POCUS on diagnostic accuracy by a bicentric, randomized, and controlled study.

## Methods and analysis

### Design

It will be a randomized, controlled, open and interventional study. POCUS will be added on top of the usual diagnosis procedure in the intervention group while it will not be used in the control group. The two recruiting centres are a university hospital and a more rural community hospital, this pragmatic approach intends to validate the added diagnostic value of POCUS in various settings.

### Objectives

To determine the diagnostic efficacy of POCUS in patients consulting in the ED for acute abdominal pain by comparing the rate of exact diagnostic between the two arms (with or without POCUS), according to the index diagnostic established by an adjudication committee. The diagnosis will be the one given by the physician before he has any access to the results of complementary examination performed in radiology.

### Participants

The included patients will be adults admitted for acute abdominal pain.

#### Inclusion criteria

Patients older than 18 years

Admitted in the ED or Nantes University Hospital or La Roche/Yon Hospital

Admitted for abdominal pain lasting for less than 5 days

Presence in the ED at that time of an EP trained in POCUS

#### Exclusion criteria

Documented end-of-life with a do-not-resuscitate order

Immediate need of life-support therapy

Patient sent to the ED by an out-of-hospital practitioner

Unable to speak and understand French

Pregnant and breast-feeding women

Patients non-affiliated to social security

Patient under guardianship

#### Drop out criteria

Patient’s death

Withdrawal of consent

### Intervention

In the control group, the diagnosis will be established after clinical examination and reception of biological analysis results. In the interventional group, a POCUS performed in the ED by a local investigator will be added and the diagnosis will be established after a clinical exam, biological analysis reception and POCUS. POCUS will only be performed by physicians who have completed a validated training program.

Furthermore, before study initiation, refresh sessions focused on acquisition techniques and pathological findings will be organized in the two participating ED. They will include hands-on sessions and presentations of pathological loops and images. Such refresher courses have been efficient to increase the overall confidence of operators [11].

### Description of POCUS

POCUS, performed in B mode only with a curvilinear probe, will assess the major spots and search for main anomalies (Table 1). It will be performed using Mindray® ME8 or TE7 or Philips® CX50 on a patient in a lying position. The following spots will be explored:Epigastric sagittal view to explore the aorta.Oblique view of the right lateral wall to explore the gallbladder, the Morrison pouch and the right kidney.Oblique view of the left lateral wall to explore the Kohler pouch and the left kidney.Hypogastric transversal and sagittal to explore the bladder, the Douglas pouch and the ovaries in women.Transversal view of the right lower quadrant in search of the appendix.Transversal exploration of the anterior abdominal wall in search of dilated bowel loops.

**Table 1 Tab1:** Spots and focussed anomalies visualized by POCUS in echoPAIN study

Organ	Pathologic finding (illness)
Abdominal aorta	Aneurysm (dilated aorta) Aortic dissection (presence of a flap)
Gallbladder	Cholelithiasis (presence of lithiasis) cholecystitis (Murphy sign, wall thickening and presence of lithiasis)
Kidneys	Renal colic (hydronephrosis)
Bladder	Dilated bladder
Peritoneum (cul-de-sac)	Presence of free fluid in the peritoneal pouches
Small bowel loops	Bowel obstruction (dilated, incompressible loops with back-and-forth liquid movements)
Appendix	Appendicitis (non-compressible appendix with diameter > 6 mm)
Ovaries	Ovarian cysts or mass

### Adjudication committee

An adjudication committee will be established, involving three independent experts in emergency medicine, radiology, and abdominal surgery. They will review all data from case report forms including routine diagnosis procedures (clinical, radiological and laboratory tests) and will determine the index diagnosis which will be used for the analysis.

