### Endpoints

#### Primary endpoint

Comparison of the rate of exact diagnostic after clinical exam and biological results with POCUS (interventional arm) or without (control arm) according to the adjudication committee diagnostic.

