### Allocation concealment mechanism

POCUS results will be concealed in the files transmitted to the adjudication committee

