### Data management

eCRFs will be used via a web-based interface. All data will be stored in Nantes University Hospital’s secured databases. The data management team will be responsible for the entire process. Data will be anonymized with an incremental number assigned to each patient. The final database will be available only to the adjudication committee.

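### The stated concealment rule withholds only POCUS results from the adjudication committee, not the physician's diagnosis under test or the arm, which leaves the primary endpoint open to review bias

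*Protocol article*

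**What the plan says.** Four parts of the protocol article bear on this point.

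- **What is judged.** Objectives: "The diagnosis will be the one given by the physician before he has any access to the results of complementary examination performed in radiology". In the POCUS arm, according to Intervention, "the diagnosis will be established after a clinical exam, biological analysis reception and POCUS".
- **How it is judged.** Under Primary endpoint the outcome is the "Comparison of the rate of exact diagnostic after clinical exam and biological results with POCUS (interventional arm) or without (control arm"), with exactness decided against the committee's diagnosis.
- **What the committee sees.** Adjudication committee: "They will review all data from case report forms including routine diagnosis procedures (clinical, radiological and laboratory tests) and will determine the index diagnosis". Under Data management, "eCRFs will be used via a web-based interface" and "The final database will be available only to the adjudication committee".
- **What is hidden from it.** The only statement is under Allocation concealment mechanism: "POCUS results will be concealed in the files transmitted to the adjudication committee".

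On blinding in general, Design states: "It will be a randomized, controlled, open and interventional study".

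**The concern.** The committee's diagnosis is the reference standard for the primary endpoint, and the physician's pre-radiology diagnosis is the result measured against it. The reference should be set without knowledge of that result. The protocol gives a broad access rule with one narrow exception, and the exception does not cover the result under test.

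Two things are at stake. First, experts who can read a working diagnosis may lean towards confirming it, above all where no later test settles the question. Second, in the POCUS arm the working diagnosis is made after the scan, so reading it can pass on the scan's conclusion even when the scan report is removed. The concealment rule shows that the authors wanted a reference independent of POCUS. As worded, it does not secure one.

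Because the trial is open, blinded adjudication is the main safeguard on this endpoint. The analysis cannot remove the influence once the committee has seen the diagnosis.

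**Working it through.** **Step 1. The sections side by side.**

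| Item | Open to the committee? | Withheld from the committee? |
|---|---|---|
| Clinical, laboratory and radiological data | Yes, named under Adjudication committee | No |
| POCUS results | Would fall under all CRF data | Yes, under Allocation concealment mechanism |
| Physician's pre-radiology diagnosis | By inference: it is the primary-endpoint variable and eCRFs are used | Not stated anywhere |
| Allocated arm | By inference, as above | Not stated anywhere |

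All CRF data less the POCUS results leaves the physician's diagnosis inside what the committee may read.

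**Step 2. Reproduce the plan's own figure.** Inputs from Sample size calculation: 57% and 74%, alpha 0.05, power 80%, 244 patients. Allocation is 1:1 (Randomization). Sidedness is not stated; two-sided is assumed. The mean rate is (0.57 + 0.74)/2 = 0.655.

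n per arm = [1.960·√(2·0.655·0.345) + 0.8416·√(0.57·0.43 + 0.74·0.26)]² / 0.17² = 121.6, rounded up to 122, so 244 in total. This matches. Power at 122 per arm is 80.1%.

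**Step 3. Illustrate the possible effect.** Let a be the share of physicians' wrong diagnoses that the committee adopts as the reference. The documents give no value for a, so every value below is an assumption. The observed rate becomes p + a(1 − p). The chance of a significant result in favour of POCUS is Φ[(d − 1.960·SE₀)/SE₁], where d is the difference in observed rates, SE₀ is the standard error under the pooled null and SE₁ the unpooled one. This is the simple comparison of two proportions that underlies the sample size, without the centre term of the planned mixed model.

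*Same a in both arms, true rates 57% and 74%.* The difference becomes 17(1 − a) points. For a = 10%: rates 0.57 + 0.1·0.43 = 0.613 and 0.74 + 0.1·0.26 = 0.766; d = 0.153, SE₀ = 0.0592, SE₁ = 0.0584; Φ(0.631) = 73.6%.

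| a | Observed rates | Difference (points) | Power |
|---|---|---|---|
| 0 | 57.0% vs 74.0% | 17.0 | 80.1% |
| 5% | 59.2% vs 75.3% | 16.2 | 77.0% |
| 10% | 61.3% vs 76.6% | 15.3 | 73.6% |
| 20% | 65.6% vs 79.2% | 13.6 | 66.3% |
| 30% | 69.9% vs 81.8% | 11.9 | 58.5% |

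*Adoption in the POCUS arm only, no true effect (57% in both arms).* For a = 20%: 0.57 + 0.2·0.43 = 0.656; d = 0.086, SE₀ = 0.0624, SE₁ = 0.0621; Φ(−0.583) = 28.0%. The opposite tail adds 0.04%.

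| a | Spurious difference (points) | Significant in favour of POCUS (nominal 2.5%) | Two-sided type I error (nominal 5%) |
|---|---|---|---|
| 5% | 2.2 | 5.3% | 6.3% |
| 10% | 4.3 | 10.1% | 10.5% |
| 20% | 8.6 | 28.0% | 28.0% |

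Equal adoption inflates both accuracy rates and shrinks the difference. Unequal adoption can create a difference where there is none.

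**The case against.** The strongest reply is that the article never says the committee reads the physician's diagnosis. It speaks of files transmitted to the committee, which suggests a prepared dossier. The examples it gives are diagnostic evidence, not opinions. The full protocol or a committee charter may define the dossier more tightly. This stands in part: that the diagnosis and the arm reach the committee is an inference. But the article is not merely silent. It states an access rule and a single exception, and on its face that exception leaves the diagnosis visible.

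Some stronger readings go further than the text allows:

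- **That the access and concealment statements contradict each other.** They read naturally as a rule and its exception. The Data management sentence fits less well, because it carries no exception. It may, however, mean access only after adjudication; the article does not say.
- **That the committee can certainly work out the arm from POCUS duration, difficulty or contribution.** These appear only as secondary endpoints, and no CRF layout is shown. The hidden POCUS results could be read as the whole POCUS section, and the section's heading suggests an intention to hide the arm.
- **That this is incorporation bias.** That term fits only if the committee uses the physician's diagnosis as evidence. Mere sight of it is review bias.
- **That a false benefit is to be expected.** That case needs the committee to know or infer that POCUS was used. Equal adoption in both arms works against POCUS.

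There is also a real counterweight. The three experts are independent, come from different specialties and see the radiology that the judged diagnosis precedes. This limits anchoring where imaging is decisive, and less so where it is absent or inconclusive.

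**Conclusion.** The point holds as a defect in the wording of the adjudication safeguard for the primary endpoint. Followed literally, the protocol lets the reference diagnosis be set with sight of the diagnosis it must judge, and in the POCUS arm this can undo the concealment of the scan.

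The size and direction of any bias cannot be derived from the documents. On assumed adoption shares, power falls from 80% to between 77% and 58% (5% to 30% in both arms), or the two-sided type I error rises to between 6% and 28% (5% to 20% in the POCUS arm only, no true effect). The second range is conditional on the committee knowing or inferring POCUS use. These figures show sensitivity and are not forecasts. The planned sample size itself reproduces and is not in question.

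**What to change.** Reword Allocation concealment mechanism, and align Adjudication committee and Data management with it, so that:

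1. the committee's file excludes the physician's pre-radiology diagnosis, the allocated arm, and every POCUS-derived field and mention, including those in free text;
2. the committee records and locks its index diagnosis first;
3. agreement with the physician's diagnosis is scored afterwards, blind to arm, by existing staff;
4. the committee's access to the final database does not bypass these limits.

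If the full protocol already provides this, one clarifying sentence is enough. The change remains useful for any case not yet adjudicated.

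The cost is data-management effort to filter the eCRF export and redact free text. The sample size and patient care do not change.

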### Endpoints

#### Primary endpoint

Comparison of the rate of exact diagnostic after clinical exam and biological results with POCUS (interventional arm) or without (control arm) according to the adjudication committee diagnostic.

#### Secondary endpoints

Comparison between the two groups:Delay between admission and diagnosticDuration of ED stayDiagnostic performances for non-specific abdominal painPrescription of biological and radiological exams during the ED stayHospitalization rateRehospitalization rateIn the interventional group (with POCUS):Diagnostic concordance between POCUS and radiological US if performedContribution of POCUS to the diagnosticDuration and self-assessed difficulty of POCUS

### Randomization

Patients will be randomized 1:1 to POCUS or control group by a computed-based program in random block sizes and stratified by centres.

### Recruiting centres

The recruiting centres will be the ED of Nantes University hospital and of La Roche/Yon hospital.

### Allocation concealment mechanism

POCUS results will be concealed in the files transmitted to the adjudication committee

### Implementation

The implementation is scheduled as follows:Recruitment of emergency physicians with validated ultrasound skills (national training program)Information of the registered nurses and other emergency physicians on the onset of the studyImplementation of the whole documents and of the patient’s pathways in the two ED by the local research teams

### Monitoring

A monitoring process will be performed in the two sites in order to control the validity of data. An audit by the public health authorities could be done.

### Amendments

According to the French law, possible amendments would be submitted to the ethics committee before being transcribed in a new version of the protocol.

### Sample size calculation

According to Lindelius [7], a correct diagnosis has been reached in 56.8% of patients consulting to the ED for acute abdominal pain after the clinical exam and biological results. The hypothesis is based on an improvement of 30% of diagnostic accuracy by POCUS. Jang [10] demonstrated an improvement of diagnostic accuracy by 45% while Lindelius by 8% [7, 8]. A correct diagnostic rate of 57% is expected in the control group and 74% in the intervention group. With a 0.05 alpha risk and a 80% power, 244 patients will be required. A 5% attrition rate (patients randomized but presenting exclusion criteria) is expected; thus, 256 randomized patients are needed for this study.

### Data management

eCRFs will be used via a web-based interface. All data will be stored in Nantes University Hospital’s secured databases. The data management team will be responsible for the entire process. Data will be anonymized with an incremental number assigned to each patient. The final database will be available only to the adjudication committee.

### Monitoring

Monitoring will be performed both by electronic surveillance of recruitment and data quality. It will be done by the Clinical Research Department of Nantes University Hospital.

### Statistical analysis

Baseline characteristics for each group will be descriptively presented using frequencies and percentages for categorical variables and means and SDs (or median and IQR if appropriate) for continuous variables. An intermediate analysis will not be performed. The primary endpoint (rate of exact diagnostic) will be compared between the two groups (with or without POCUS) using a mixed model taking into account the recruiting centre (factor of stratification of randomization). The delays will be compared by a mixed linear generalized model adjusted on the recruiting centres for the same reason as for the primary endpoint. Sensitivity, specificity and positive and negative predictive values will be estimated with their 95% confidence intervals. The number of biological exams will be compared between the two groups using a Poisson model. The rates of readmission and hospitalization will be compared using a logistic generalized mixed model adjusted on the centre.

In the interventional group (with POCUS), the concordance between the POCUS and ultrasound performed by a radiologist will be assessed by Kappa coefficient. Duration and self-assessed difficulty of POCUS will be described by means, SDs, medians, minimums and maximums.

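### The mixed models have centre as their only grouping factor, but there are only two centres: fit centre as a fixed effect (minor, no cost)

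*Protocol article*

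**What the plan says.** The Statistical analysis section of the protocol article compares the primary endpoint "using a mixed model taking into account the recruiting centre (factor of stratification of randomization". It handles the delays with a mixed generalized linear model, giving the same reason for including centre. For two further outcomes: "The rates of readmission and hospitalization will be compared using a logistic generalized mixed model adjusted on the centre". No other grouping factor, such as the physician, is named, and nothing is said about what happens if a variance estimate is zero.

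The number of centres is fixed. Design: "The two recruiting centres are a university hospital and a more rural community hospital". Recruiting centres: "The recruiting centres will be the ED of Nantes University hospital and of La Roche/Yon hospital". Randomization: "Patients will be randomized 1:1 to POCUS or control group by a computed-based program in random block sizes and stratified by centres".

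**The concern.** A mixed model needs at least one random effect, and centre is the only candidate in the text. Two centres, picked to represent two types of hospital, are not a sample from which a between-centre variance can usefully be estimated. When the estimate lands on zero, the random intercept vanishes and the fit equals the unadjusted comparison.

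The section's reason for including centre is that randomization was stratified on it. Under this model, whether the stratum is actually adjusted for depends on where a poorly determined variance estimate falls. In an open trial, a singular fit on the primary endpoint also invites a choice of model after the data have been seen.

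**Working it through.** **Inputs from the article.** The Sample size calculation section assumes exact-diagnosis rates of 57% (control) and 74% (POCUS) and sets the size as follows: "With a 0.05 alpha risk and a 80% power, 244 patients will be required". There are two centres, with 1:1 allocation stratified by centre.

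**Inputs that are assumptions.** The article gives neither the difference between centres nor the recruitment split. The ranges used are centre log-odds differences of 0 to 1.0 and splits of 50:50 and 70:30. Around the mean rate of (57% + 74%)/2 = 65.5%, a log-odds difference of 0.4 is about 9 percentage points and 0.8 is about 18.

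**Step 1: reproduce the planned size.** Two-sided test, pooled variance under the null, no continuity correction:

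n per arm = [1.960·√(2·0.655·0.345) + 0.842·√(0.57·0.43 + 0.74·0.26)]² / 0.17² = 121.6, so 122 per arm and 244 in total, with power 0.801. The stated figure reproduces. It does not depend on how centre is modelled.

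**Step 2: information on the variance.** Two centres give 1 degree of freedom. Even if each centre's level were known without error, the 95% interval for the between-centre SD would run from √(1/χ²₀.₉₇₅) to √(1/χ²₀.₀₂₅) times the estimate, that is from 0.45 to 31.9 times.

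**Step 3: how often the variance is zero.** Trials of 244 patients were simulated at 57% and 74% and fitted by maximum likelihood with a random-intercept logistic model (400 runs per cell). A fit counts as zero when the random intercept adds nothing to the likelihood or its SD is below about 0.018.

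| Centre log-odds difference | 50:50 split | 70:30 split |
|---|---|---|
| 0 | 83% | 88% |
| 0.2 | 72% | 81% |
| 0.4 | 48% | 52% |
| 0.6 | 23% | 30% |
| 0.8 | 6% | 11% |
| 1.0 | 1.5% | 4% |

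A second simulation over the same splits gave 88–90% at 0, 48–61% at 0.4 and 8–9% at 0.8.

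**Step 4: what a collapse costs.** Take 122 per arm, equal centres, a common odds ratio, and arm rates averaging 57% and 74%.

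- Unadjusted: log-OR = logit(0.74) − logit(0.57) = 0.764. Variance = 1/(122·0.57·0.43) + 1/(122·0.74·0.26) = 0.0760. z = 0.764/0.276 = 2.771. Power ≈ Φ(2.771 − 1.960) = 79.1%.
- Adjusted, 10-point centre difference (log-odds 0.46): log-OR 0.773, variance 0.0770, z = 2.786, power 79.5%. Loss from collapse: 0.4 points.
- Adjusted, 20-point difference (log-odds 0.94): log-OR 0.801, variance 0.0801, z = 2.831, power 80.8%. Loss from collapse: 1.7 points.

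**Step 5: mixed against fixed, directly.** In the Step 3 simulations, power with fixed centre was within 0.5 points of the mixed model in every cell. Under the null (57% in both arms, 50:50 split, 1,500 runs), type I error at differences 0, 0.4 and 0.8 was 0.046, 0.045 and 0.069 for the mixed model and 0.046, 0.047 and 0.069 for fixed centre. The 0.069 is simulation noise: 200,000 runs of the fixed-centre Wald test gave 0.048, 0.048 and 0.051.

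**The case against.** The strongest reply is that no conclusion of the trial would change. Allocation is balanced within centre, so the arms are comparable whichever model is fitted, and Step 5 shows mixed and fixed centre performing alike. This stands, and it sets the severity.

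The collapse is also largely self-limiting. The variance goes to zero mainly when the centres barely differ, and then there is little to adjust for. A 20-point difference lies between the 0.8 and 1.0 rows of the table, where collapse occurs in 1.5–6% of fits (50:50) or 4–11% (70:30). The hospitals were chosen to be unlike, which makes larger differences more plausible and collapse less frequent. This also stands.

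Thirdly, the text does not say that centre is random, and adjusting on centre is wording also used for covariates. The article condenses a fuller document, and an analysis plan not shown could specify a fixed term or a fallback. That is fair, so random centre is put forward as the natural reading and not as a stated fact. The point survives because the article does fix the model class for the primary endpoint.

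Two stronger readings are tempting and are not supported:

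- A reader might infer that losing the adjustment inflates the variance of the treatment effect. That is true of a risk difference. On the log-odds scale of a logistic model it goes the other way: the unadjusted-to-adjusted variance ratios from Step 4 are 0.987 at 10 points and 0.949 at 20. The small power loss comes from the log-odds ratio being pulled towards zero.
- A reader might infer that a fixed centre term would show how POCUS performs in each hospital, which the Design section's aim of covering varied settings would invite. A fixed main effect assumes one common arm effect. Centre-specific effects need an interaction or separate estimates, and these can be reported under either model.

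**Conclusion.** The concern holds as a minor point about specification. With two purposively chosen centres, a random centre effect cannot be estimated usefully, and unless the centres differ strongly it drops out of a substantial share of fits. The documents do not support calling the primary analysis invalid, biased or underpowered: the sample size stands at 244, no material bias arises, and the power at stake is about 0.4 to 1.7 points and only when the fit collapses. The conclusion rests on reading centre as the random effect, and the collapse rates rest on centre differences and splits that the article does not give. The reason to act is that a fixed term guarantees the adjustment the section says it wants and removes a possible post hoc choice on the primary endpoint.

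**What to change.** State that centre is fitted as a fixed effect. For exact diagnosis, readmission and hospitalization, use logistic regression with arm and centre, or a Mantel-Haenszel analysis stratified by centre. Include a fixed centre term in the delay models. Settle this before the database is locked. If the full analysis plan already does this, only the article's wording is at issue.

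The cost is one sentence and one model parameter, with no change to data or sample size. A risk difference standardised over centre, a gamma model for the delays and arm effects reported by centre are optional extras and not needed to resolve this point.

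### The admission-based delay endpoints include time before randomisation, and the stated model adjusts for centre only: a baseline covariate could gain precision, by an amount the protocol does not let one estimate

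*Protocol article*

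**What the plan says.** The Secondary endpoints section of the protocol article lists the delay from admission to diagnosis and the length of ED stay. The abstract's Methods also name diagnostic delay and "duration of ED stay". Only the delay has a written starting point, which is admission. For ED stay the start is implied by the term.

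The Statistical analysis section fixes the model: "The delays will be compared by a mixed linear generalized model adjusted on the recruiting centres". It says the reason is the same as for the primary endpoint, which is to be analysed "using a mixed model taking into account the recruiting centre (factor of stratification of randomization"). Centre is the only adjustment named. No link function or error distribution is given.

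On sequence, the Inclusion criteria require a patient "Admitted for abdominal pain lasting for less than 5 days", and also "Presence in the ED at that time of an EP trained in POCUS". The Randomization section states: "Patients will be randomized 1:1 to POCUS or control group by a computed-based program in random block sizes and stratified by centres". It does not say how long after admission this happens.

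**The concern.** Randomisation cannot come before admission, because admission is a condition of eligibility. Each admission-based time is therefore the sum of an interval before allocation and an interval after it. The first is a genuine baseline quantity: it is complete when the patient is allocated, and the arm cannot change it. Under a model with centre alone, all within-centre variation in the first interval goes into the residual.

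The reason given for adjusting on centre is that it is the stratification factor. That reason is sound, but it was carried over from the primary endpoint, which has no measurable pre-randomisation component. The time endpoints do. At stake is the width of the intervals on two secondary endpoints for which the trial was not sized, so their precision depends on what the analysis can extract from a number of patients fixed for another purpose.

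**Working it through.** **The plan's own figure.** The only calculation in the article is for the primary endpoint: "A correct diagnostic rate of 57% is expected in the control group and 74% in the intervention group", alpha 0.05, power 80%. With pooled variance, two sides and no continuity correction:

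- n per arm = [1.960 × √(2 × 0.655 × 0.345) + 0.842 × √(0.57 × 0.43 + 0.74 × 0.26)]² / 0.17² = 121.6, rounded up to 122.
- The total is 244, as stated. Power at 122 per arm is 80.1%.

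Nothing in this figure involves the time endpoints, so the present point does not touch it.

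**Set-up.** Let W be the time from admission to randomisation, Y the time from randomisation to diagnosis or ED exit, and T = W + Y the outcome. Let k = SD(W)/SD(Y) and r = corr(W, Y). The documents give neither k nor r, so both are assumed. An identity link is also assumed.

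- Share of the variance of T explained by W: R² = (k + r)² / (k² + 1 + 2rk). With r = 0 this is k² / (k² + 1).
- Standard error after adjusting for W, relative to before: √(1 − R²).
- Number of unadjusted patients giving the same precision as 244 adjusted: 244 / (1 − R²).

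**Independent intervals (r = 0).**

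| k | R² | SE multiplier | Equivalent N | Power, if 80% unadjusted |
|---|---|---|---|---|
| 0.25 | 0.0625/1.0625 = 0.06 | 0.97 | 259 | 82% |
| 0.50 | 0.25/1.25 = 0.20 | 0.89 | 305 | 88% |
| 0.75 | 0.5625/1.5625 = 0.36 | 0.80 | 381 | 94% |
| 1.00 | 1/2 = 0.50 | 0.71 | 488 | 98% |

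For orientation, SDs of 45 and 180 minutes give k = 0.25, and 90 and 120 minutes give k = 0.75. These minutes are assumptions too.

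**Correlated intervals.** The result depends strongly on r:

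- r = −0.3, k = 0.25: R² = 0.0025/0.9125 = 0.003, SE multiplier 0.999.
- r = −0.3, k = 0.50: R² = 0.04/0.95 = 0.04, SE multiplier 0.98.
- r = −0.5, k = 0.50: R² = 0, no gain.
- r = +0.3, k = 0.25: R² = 0.3025/1.2125 = 0.25, SE multiplier 0.87.
- r = +0.3, k = 0.50: R² = 0.64/1.55 = 0.41, SE multiplier 0.77.

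A positive correlation is plausible if crowding lengthens both intervals. A negative one is plausible if work-up already begins while the patient waits to be randomised. The article supports neither.

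**The case against.** The strongest case against is that nothing here is an error. A randomised comparison of admission-based times, adjusted for the stratification factor, is valid, and an admission-based clock is a legitimate clinical measure. Extra covariates for secondary endpoints are ordinary content of a statistical analysis plan, which may exist and is not shown. The article does not say that centre will be the only covariate. The trained-physician criterion can be read as presence around the time of admission; if patients are enrolled near triage, the early interval may be too short to matter. The variance algebra also holds only on an identity scale, and the link is unstated.

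Most of this stands, and it limits the size and weight of the point. It does not remove it, because the article does commit to a model, an adjustment and a reason, and that model can be improved at very little cost.

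A reader might also infer that a chance imbalance in waiting time could create or hide a POCUS effect. With 122 per arm and an assumed SD of 45 to 90 minutes, the standard error of the between-arm difference in mean wait is SD × √(2/122), about 5.8 to 11.5 minutes. But the unadjusted standard error and type I error already allow for that variation, so it is not a separate harm. It is the same loss of precision seen from another side.

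**Conclusion.** The point holds as an optional efficiency gain on secondary endpoints. The delay to diagnosis, and by implication ED stay, contains time that allocation cannot affect, and the stated model leaves its variation in the residual. With k from 0.25 to 0.75, independence and an identity link, the standard error would fall by about 3% to 20%. Under a moderate negative correlation, or a short early interval, it would hardly fall at all.

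Two stronger readings are not supported. The first is that the planned comparison is biased: randomisation balances the early interval in expectation. The second is that the loss is known to be material: the article gives no time distribution, no moment of randomisation and no written start for ED stay, so any percentage follows from the assumptions and not from the plan.

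**What to change.** In the Statistical analysis section, keep both endpoints as defined and prespecify the admission-to-randomisation interval as a baseline covariate beside centre in the delay and ED-stay models. State its functional form and the link function. Report time from randomisation, adjusted for centre, as a supporting analysis.

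The covariate is preferable to subtraction as the main adjustment because the data then set its coefficient. Subtraction forces the coefficient to 1 and can lose precision: at k = 0.50 and r = −0.5, in units where Var(Y) = 1, the unsubtracted outcome has variance 0.25 + 1 − 0.50 = 0.75, smaller than that of Y.

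The cost is small. Admission time is already needed for the delay endpoint. The time of allocation must be kept from the randomisation program and linked to the analysis file; the article does not say that this is done. The model gains one degree of freedom for a linear term and one functional-form choice. The change should be fixed before the time data are analysed by arm.
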